**Health hygiene education intervention**

Lack of knowledge on the transmission and prevention methods of STH infections is common factor in affected population groups of Latin America [27]. Therefore, the specific objectives of the health hygiene education intervention are:

i) To implement a gender-specific health hygiene education strategy which will result in a sustainable intervention that encourages the pro-active role of both teachers and students.

ii) To encourage changes in attitudes and practices with the aim of keeping the level of parasite infection low, through increased knowledge.

iii) To identify modifiable gender-specific behavioural and social determinants which favour the acquisition and transmission of STH infections to inform prevention activities.

Workshops will be organized for and by Grade 5 teachers to train them on the health hygiene education strategy. The education material will be provided by the Pan American Health Organization (in Spanish) and will be adapted to the local culture. The health hygiene education intervention will take into account the gender-specific perceptions, values, social constructs, and beliefs of students and teachers relevant to STH infections in order to maximize behavioural changes. After the workshop, Grade 5 teachers will be able to implement the health hygiene education intervention in their classroom and engage their students. Bi-monthly visits with the teacher by our research team and once monthly with the class will be performed to monitor the application of the education program during the 4-month follow-up period. Specifically, the intention of the health hygiene education program is to modify key gender-specific modifiable behavioural determinants that have been shown to be associated with STH infections from our review of the literature:

i) Not using soap for hand washing [28-30]

ii) Not hand washing (no reference to the use of soap) [31-33]

iii) Eating unpeeled or unwashed fruits [31, 34]

iv) Walking barefoot [30, 33]

v) Open air defecation [33-35]

vi) General unhygienic behaviours [36]

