**Measurements**

Weight of the child will be measured using a portable flat scale (seca 869, seca corp., Baltimore, MD) and a mobile stadiometer (seca 217, seca corp., Baltimore, MD) will be used to measure their height. Individual risk factors, potential confounding variables, level of knowledge on STH transmission, and behavioural determinants will be measured using an interviewer-administered questionnaire at baseline. After the 4-month follow-up period, the same questionnaire will be re-administered.

Stool specimens will be obtained in small plastic containers at baseline and at the end of the 4-month follow-up period by trained research personnel. Trained technologists will use the Kato-Katz method to examine the specimens for the presence, species and intensity of STH eggs [37]. This technique is the preferred method for assessment of the prevalence and intensity of intestinal parasitic infections in the field [4, 38]. The technologists will be blinded to the group assignment.

Data collection activities during fieldwork will be regularly supervised. Measurement bias will be kept to a minimum by ensuring calibration of study instruments (balance and scale), quality control assessments, and daily review of completed questionnaires. At each assessment, the coordinator will check all completed forms immediately after data collection at the end of each day. Entries on the questionnaires will be checked and if discrepancies or unclear answers appear, a discussion and explanation of the question and eligible answers will take place to avoid making errors the next day. Corrections will be made, if warranted. These types of errors should be kept to a minimum, as there will be a pre-testing phase with all interviewers to ensure correct data collection procedures and records. The consistency of the microscopic readings will be verified both during the examination and afterward as follows. The consistency of egg counting will be evaluated among the laboratory technologists using standard quality control methods [38]. The laboratory supervisor will read 10% of the slides of each microscopist without prior knowledge of the results. In the case of a discrepancy larger than 10%, the two readers will discuss the slides and further slides will be examined to avoid repeated errors. It should be noted that trained microscopists from our previous study will perform the examinations. They have an excellent performance record.

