| **14** | | ¿En casa tomas agua directo o tratada (hervida o clorada)? | | \| **⃞** \| Directo \| (1) \| **⃞** \| Tratada \| (0) \| **⃞** \| *No sabe* \| (99) \| \| --- \| --- \| --- \| --- \| --- \| --- \| --- \| --- \| --- \| | |
| **15** | | ¿Tu baño se ubica adentro o afuera de tu casa? | | \| **⃞** \| Adentro \| (1) \| **⃞** \| Afuera \| (0) \| **⃞** \| *No sabe* \| (99) \| \| --- \| --- \| --- \| --- \| --- \| --- \| --- \| --- \| --- \| | |
| **16** | | ¿Tu baño está conectado a tubo de desagüe, a caño, a río, o a pozo ciego? | | \| **⃞** \| Desagüe \| (0) \| **⃞** \| Río \| (2) \| \| --- \| --- \| --- \| --- \| --- \| --- \| \| **⃞** \| Caño \| (1) \| **⃞** \| Pozo ciego o silo \| (3) \| \| **⃞** *No sabe* (99) \| \| \| \| \| \| | |
| **17** | | ¿Te bañas en el río Itaya – siempre, a veces, o nunca? | | \| **⃞** \| Siempre \| (0) \| **⃞** \| Nunca \| (2) \| \| --- \| --- \| --- \| --- \| --- \| --- \| \| **⃞** \| A veces \| (1) \| **⃞** \| *No sabe* \| (99) \| | |
| **18** | | ¿Haces el dos en campo abierto (huerta o patio) - siempre, a veces, o nunca? | | \| **⃞** \| Siempre \| (0) \| **⃞** \| Nunca \| (2) \| \| --- \| --- \| --- \| --- \| --- \| --- \| \| **⃞** \| A veces \| (1) \| **⃞** \| *No sabe* \| (99) \| | |
| **19** | | ¿Te limpias con papel higiénico cuando haces el dos - siempre, a veces, o nunca? | | \| **⃞** \| Siempre \| (0) \| **⃞** \| Nunca \| (2) \| \| --- \| --- \| --- \| --- \| --- \| --- \| \| **⃞** \| A veces \| (1) \| **⃞** \| *No sabe* \| (99) \| | |
| **20** | | **A-** ¿Te lavas las manos después de ir al baño – siempre, a veces, o nunca?  **B-** ¿Cómo te lavas las manos después de ir al baño -con agua sola o jabón y agua?   \| **⃞** *No aplica (NA)* \| \| --- \|   **C-** ¿Si es con jabón, lo usas siempre, a veces, o nunca?   \| **⃞** *No aplica (NA)* \| \| --- \| | | \| **⃞** \| Siempre \| (0) \| **⃞** \| Nunca \| (2) \| \| --- \| --- \| --- \| --- \| --- \| --- \| \| **⃞** \| A veces \| (1) \| **⃞** \| *No sabe* \| (99) \|  \| **⃞** \| Agua \| (0) \| **⃞** \| Jabón y agua \| (1) \| **⃞** \| *No sabe* \| (99) \| \| --- \| --- \| --- \| --- \| --- \| --- \| --- \| --- \| --- \|  \| **⃞** \| Siempre \| (0) \| **⃞** \| Nunca \| (2) \| \| --- \| --- \| --- \| --- \| --- \| --- \| \| **⃞** \| A veces \| (1) \| **⃞** \| *No sabe* \| (99) \| | |

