| **21** | | **A-** ¿Te lavas las manos antes de comer – siempre, a veces, o nunca?  **B-** Cómo te lavas las manos antes de comer -con agua sola o jabón y agua?   \| **⃞** *No aplica (NA)* \| \| --- \|   **C-** ¿Si es con jabón, lo usas siempre, a veces, o nunca?   \| **⃞** *No aplica (NA)* \| \| --- \| | | \| **⃞** \| Siempre \| (0) \| **⃞** \| Nunca \| (2) \| \| --- \| --- \| --- \| --- \| --- \| --- \| \| **⃞** \| A veces \| (1) \| **⃞** \| *No sabe* \| (99) \|  \| **⃞** \| Agua \| (0) \| **⃞** \| Jabón y agua \| (1) \| **⃞** \| *No sabe* \| (99) \| \| --- \| --- \| --- \| --- \| --- \| --- \| --- \| --- \| --- \|  \| **⃞** \| Siempre \| (0) \| **⃞** \| Nunca \| (2) \| \| --- \| --- \| --- \| --- \| --- \| --- \| \| **⃞** \| A veces \| (1) \| **⃞** \| *No sabe* \| (99) \| | |
| **22** | | **A-** ¿Cuál es tu fruta favorita?  **B-** ¿Lavas tus frutas antes de comer - siempre, a veces, o nunca? | | Fruta: ………………………………….   \| **⃞** \| Nunca \| (0) \| **⃞** \| Siempre \| (2) \| \| --- \| --- \| --- \| --- \| --- \| --- \| \| **⃞** \| A veces \| (1) \| **⃞** \| *No sabe* \| (99) \| | |
| **26** | | ¿Caminas descalzo(a) – siempre, a veces, o nunca? | | \| **⃞** \| Nunca \| (0) \| **⃞** \| Siempre \| (2) \| \| --- \| --- \| --- \| --- \| --- \| --- \| \| **⃞** \| A veces \| (1) \| **⃞** \| *No sabe* \| (99) \| | |
| **27** | | ¿Cuándo estás en casa, usas zapatos o sandalias? | | \| **⃞** \| No usa \| (0) \| **⃞** \| Zapato \| (2) \| \| --- \| --- \| --- \| --- \| --- \| --- \| \| **⃞** \| Sandalias \| (1) \| **⃞** \| *No sabe* \| (99) \| | |
| **28** | | ¿En qué actividades del día estas descalzo(a)?   \| **⃞** *No aplica (NA)* \| \| --- \| | | A- Actividad: ………..………………………………….  B- Actividad: ………..………………………………….  C- Actividad: ………..…………………………………. | |
| **29** | | **A-** ¿Tus padres o tu profesor te dieron purgante (te desparasitaron)?  **B-** ¿En caso que si, cuándo fue la última vez que te dieron purgante? | | \| **⃞** \| Si \| (1) \| **⃞** \| No \| (0) \| **⃞** \| *No sabe* \| (99) \| \| --- \| --- \| --- \| --- \| --- \| --- \| --- \| --- \| --- \|  \|  \| Meses \| **⃞** \| Más de un año (13) \| **⃞**  **⃞** \| *No sabe (99)*  No aplica (NA) \| \| --- \| --- \| --- \| --- \| --- \| --- \| | |

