| **14** | | In your house do you drink your water directly or do you treat it (boiling or bleaching)? | | \| **⃞** \| Directly \| (1) \| **⃞** \| Treated \| (0) \| **⃞** \| *Don’t know* \| (99) \| \| --- \| --- \| --- \| --- \| --- \| --- \| --- \| --- \| --- \| | |
| **15** | | At home, is your latrine inside or outside the house? | | \| **⃞** \| Inside \| (1) \| **⃞** \| Outside \| (0) \| **⃞** \| *Don’t know* \| (99) \| \| --- \| --- \| --- \| --- \| --- \| --- \| --- \| --- \| --- \| | |
| **16** | | Is your latrine connected with the sewage system, a ditch, the river, or a well? | | \| **⃞** \| Sewage \| (0) \| **⃞** \| River \| (2) \| \| --- \| --- \| --- \| --- \| --- \| --- \| \| **⃞** \| Ditch \| (1) \| **⃞** \| Well \| (3) \| \| **⃞** *Don’t know* (99) \| \| \| \| \| \| | |
| **17** | | Do you bath in the Itaya river – always, sometimes, or never? | | \| **⃞** \| Always \| (0) \| **⃞** \| Never \| (2) \| \| --- \| --- \| --- \| --- \| --- \| --- \| \| **⃞** \| Sometimes \| (1) \| **⃞** \| *Don’t know* \| (99) \| | |
| **18** | | Do you defecate (#2) in the open air – always, sometimes, or never? | | \| **⃞** \| Always \| (0) \| **⃞** \| Never \| (2) \| \| --- \| --- \| --- \| --- \| --- \| --- \| \| **⃞** \| Sometimes \| (1) \| **⃞** \| *Don’t know* \| (99) \| | |
| **19** | | Do you use toilet paper to wipe your bum after you have defecated (#2) – always, sometimes, or never? | | \| **⃞** \| Always \| (0) \| **⃞** \| Never \| (2) \| \| --- \| --- \| --- \| --- \| --- \| --- \| \| **⃞** \| Sometimes \| (1) \| **⃞** \| *Don’t know* \| (99) \| | |
| **20** | | **A-** Do you wash your hands after going to the bathroom – always, sometimes, or never?  **B-** How do you wash your hands after going to the bathroom – with water only or with soap and water?   \| **⃞** *Not applicable (NA)* \| \| --- \|   **C-** If with soap and water, do you use soap always, sometimes, or never?   \| **⃞** *Not applicable (NA)* \| \| --- \| | | \| **⃞** \| Always \| (0) \| **⃞** \| Never \| (2) \| \| --- \| --- \| --- \| --- \| --- \| --- \| \| **⃞** \| Sometimes \| (1) \| **⃞** \| *Don’t know* \| (99) \|  \| **⃞** \| Water \| (0) \| **⃞** \| Soap and water \| (1) \| **⃞** \| *Don’t know* \| (99) \| \| --- \| --- \| --- \| --- \| --- \| --- \| --- \| --- \| --- \|  \| **⃞** \| Always \| (0) \| **⃞** \| Never \| (2) \| \| --- \| --- \| --- \| --- \| --- \| --- \| \| **⃞** \| Sometimes \| (1) \| **⃞** \| *Don’t know* \| (99) \| | |

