| **21** | | **A-** Do you wash your hands before eating – always, sometimes, or never?  **B-** How do you wash your hands before eating – with water only or with soap and water?   \| **⃞** *Not applicable (NA)* \| \| --- \|   **C-** ¿ If with soap and water, do you use soap always, sometimes, or never?   \| **⃞***Not applicable (NA)* \| \| --- \| | | \| **⃞** \| Always \| (0) \| **⃞** \| Never \| (2) \| \| --- \| --- \| --- \| --- \| --- \| --- \| \| **⃞** \| Sometimes \| (1) \| **⃞** \| *Don’t know* \| (99) \|  \| **⃞** \| Water \| (0) \| **⃞** \| Soap and water \| (1) \| **⃞** \| *Don’t know* \| (99) \| \| --- \| --- \| --- \| --- \| --- \| --- \| --- \| --- \| --- \|  \| **⃞** \| Always \| (0) \| **⃞** \| Never \| (2) \| \| --- \| --- \| --- \| --- \| --- \| --- \| \| **⃞** \| Sometimes \| (1) \| **⃞** \| *Don’t know* \| (99) \| | |
| **22** | | **A-** What is your favourite fruit that you eat?  **B-** Do you was your fruits before eating - always, sometimes, or never? | | Fruit: ………………………………….   \| **⃞** \| Never \| (0) \| **⃞** \| Always \| (2) \| \| --- \| --- \| --- \| --- \| --- \| --- \| \| **⃞** \| Sometimes \| (1) \| **⃞** \| *Don’t know* \| (99) \| | |
| **26** | | Do you walk barefoot - always, sometimes, or never? | | \| **⃞** \| Never \| (0) \| **⃞** \| Always \| (2) \| \| --- \| --- \| --- \| --- \| --- \| --- \| \| **⃞** \| Sometimes \| (1) \| **⃞** \| *Don’t know* \| (99) \| | |
| **27** | | When you are at home do you prefer to use sandals or shoes? | | \| **⃞** \| Does not use any \| (0) \| **⃞** \| Shoes \| (2) \| \| --- \| --- \| --- \| --- \| --- \| --- \| \| **⃞** \| Sandals \| (1) \| **⃞** \| *Don’t know* \| (99) \| | |
| **28** | | In which activities of the day are you barefoot?   \| **⃞** *Not applicable (NA)* \| \| --- \| | | A- Activity: ………..………………………………….  B- Activity: ………..………………………………….  C- Activity: ………..…………………………………. | |
| **29** | | **A-** Did your parents or your professor gave you a deworming pill?  **B-** If yes, when was the last time they gave you such deworming pill? | | \| **⃞** \| Yes \| (1) \| **⃞** \| No \| (0) \| **⃞** \| *Don’t know* \| (99) \| \| --- \| --- \| --- \| --- \| --- \| --- \| --- \| --- \| --- \|  \|  \| Months \| **⃞** \| More than a year (13) \| **⃞**  **⃞** \| *Don’t know (99)*  Not applicable (NA) \| \| --- \| --- \| --- \| --- \| --- \| --- \| | |

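### In questionnaire items 20 and 21, occasional soap users who answer 'water' are recorded exactly like children who never use soap

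*Protocol*

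**What the plan says.** The Measurements section of the protocol says that "behavioural determinants will be measured using an interviewer-administered questionnaire at baseline", and that the same instrument is used again at four months. The questionnaire is annexed in Spanish (Annex 5) and English (Annex 6). Item 20 covers hand washing after the bathroom and item 21 hand washing before eating. Each has three parts:

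- **Part A** asks how often the child washes, without mentioning soap. In item 20: "Te lavas las manos después de ir al baño – siempre, a veces, o nunca".
- **Part B** asks how the child washes. In item 20: "Cómo te lavas las manos después de ir al baño -con agua sola o jabón y agua". In item 21: "Cómo te lavas las manos antes de comer -con agua sola o jabón y agua". The boxes are water (0), soap and water (1), don't know (99) and not applicable.
- **Part C** asks soap frequency under a condition, "Si es con jabón, lo usas siempre, a veces, o nunca", with boxes for always (0), sometimes (1), never (2), don't know (99) and not applicable.

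The English form has the same structure (part B of item 21: "How do you wash your hands before eating – with water only or with soap and water"; part C: "If with soap and water, do you use soap always, sometimes, or never"), so this is not a translation slip.

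Under Health hygiene education intervention, "Not using soap for hand washing" is item i of six behaviours that the programme aims to change. Secondary objective iv covers behavioural and social determinants of infection, re-infection and absenteeism.

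**The concern.** Part B offers two exclusive answers about a behaviour that part C treats as having three levels. A child who uses soap on some occasions can reasonably give either answer. With 'water', part C does not apply and the information that soap is sometimes used is lost.

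At stake is the quality of one exposure variable for secondary objective iv. If the recorded no-soap group contains occasional users, and their risk lies between that of never-users and always-users, the estimated association between not using soap and infection moves towards no effect. Other behaviour-frequency questions on the form (items 17, 18, 19, 20A, 21A, 22B and 26) ask always/sometimes/never directly, with no gate before them. Soap frequency, which relates to a listed target behaviour, has one.

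**Working it through.** The protocol gives no figure for this point, so there is none to reproduce. The check has two steps.

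**Step 1: which records are possible.** For a child who washes hands (part A = always or sometimes), the printed wording allows these answers to B and C:

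| True soap use | Possible record (B, C) |
|---|---|
| Always | (soap and water, always) |
| Sometimes | (soap and water, sometimes) or (water, not applicable) |
| Never | (water, not applicable) |

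The record (water, not applicable) is shared by never-users and some occasional users. Part A cannot separate them, because it concerns washing and not soap. The third box in C, 'never', belongs to no coherent record: a child who washes with soap cannot also never use it.

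**Step 2: illustration of the effect on an odds ratio.** Every input here is assumed; none is in the protocol.

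- Soap use always / sometimes / never: 30% / 40% / 30% of children who wash hands.
- Risk of infection among always-users 0.40, so odds 0.40/0.60 = 0.667.
- True odds ratios against always: sometimes 1.5 (odds 1.0, risk 0.500); never 2.0 (odds 1.333, risk 0.5714).
- f = share of occasional users who answer 'water', taken to have the average risk of occasional users.

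Risk in the recorded no-soap group = (0.30 × 0.5714 + f × 0.40 × 0.500) / (0.30 + f × 0.40). Its odds are divided by 0.667 to give the odds ratio.

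| f | Recorded no-soap group | Risk in that group | Odds ratio (true 2.0) |
|---|---|---|---|
| 0 | 30% | 0.571 | 2.00 |
| 0.25 | 40% | 0.554 | 1.86 |
| 0.50 | 50% | 0.543 | 1.78 |
| 0.75 | 60% | 0.536 | 1.73 |
| 1 | 70% | 0.531 | 1.70 |

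The recorded 'sometimes' group shrinks to match: 40% × (1 − f) = 30%, 20% or 10% of children at f = 0.25, 0.50 or 0.75. The direction of the association is kept throughout.

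**The case against.** The strongest reply is that the form already has a route for occasional users: 'soap and water' in B, then 'sometimes' in C. The 'sometimes' box suggests that 'soap and water' was meant to include them. That stands. A reader might infer that the form erases the middle category altogether, and the documents do not support this, because only those who answer 'water' are lost.

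Second, no skip instruction is printed at items 20 and 21, whereas the eligibility questions carry explicit ones. The skip is implied by the condition in C and its not-applicable box. It is the natural reading, but still an inference.

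Third, the Measurements section provides for interviewer administration, a pre-test with all interviewers, daily review of forms and discussion of unclear answers. An alert interviewer who hears 'sometimes with soap' can tick the right boxes. This may reduce the problem, but no written rule says how to code such a child, so it depends on the interviewer.

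Fourth, the illustration may overstate the loss. Occasional users who say 'water' are plausibly the rarest soap users, with risk close to that of never-users, and the odds ratio would then fall less.

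Fifth, a reader might infer that the form will hide an intervention effect, as children move from never to sometimes using soap. The documents do not support that as a stated harm. Planned statistical analyses contains no comparison of change in soap use, no behaviour-change outcome is listed among the objectives, and nothing shows that such a move is the likely early result. A child newly taught to use soap may well answer 'soap and water' and be captured.

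**Conclusion.** The point holds in a limited form. In both languages and at both survey waves, items 20 and 21 let occasional soap users who answer 'water' share a record with never-users, and this cannot be undone in analysis. The 'never' box in part C is also inconsistent with its condition.

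How many children are affected is unknown. On the assumed inputs, with a quarter to three quarters of occasional users answering 'water', an odds ratio of 2.0 would be estimated as 1.86 to 1.73. That is a modest weakening with the direction kept, and it rests entirely on assumed soap-use shares, risks and misrouting.

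The reach is one determinant under secondary objective iv. It would be wrong to infer a threat to the main result: re-infection is read from stool specimens by blinded technologists, soap use is not a named covariate in the main model, and the sample-size reasoning does not use it. Nor should the position of soap at the head of the behaviour list be read as a ranking, since the protocol states none. This is a low-priority improvement to the form.

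**What to change.** Before the planned pre-test, replace parts B and C of items 20 and 21, in Annexes 5 and 6 and for both waves, with one question put to every child whose answer to part A is always or sometimes: 'When you wash your hands, do you use soap: always, sometimes, or never?' It should stay tied to the occasion of each item (after the bathroom; before eating). Keep the don't-know and not-applicable boxes, the latter for children who never wash on that occasion. The three levels of soap use then give three distinct records, and the water versus soap-and-water split can be derived from them.

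The cost is an edit to two items in two languages, and the form becomes shorter. The one drawback is slightly less comparability with any earlier survey that used the present wording.

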**Effectiveness of a post-deworming education intervention to reduce infection and absenteeism in grade 5 school children**

**School, Child, and Interviewer Identification**

| School name  _____________________  Name of Teacher/Class  ______________________ | Name of Child:  _________________________________  Unique Id number   \|  \| \| --- \| | Name of Interviewer  _____________________  Date of Interview (dd/mm/aaaa)   \| **/ /** \| \| --- \| |
| --- | --- | --- | --- | --- |

**Eligibility requirements**

| **A** | Has the parent consented? | \| **⃞** \| Yes \| *Go to question B* \| **⃞** \| No \| *Stop interview* \| \| --- \| --- \| --- \| --- \| --- \| --- \| |
| --- | --- | --- | --- | --- | --- | --- | --- | --- |
| **B** | Has the child assented? | \| **⃞** \| Yes \| *Go to question 1* \| **⃞** \| No \| *Stop interview* \| \| --- \| --- \| --- \| --- \| --- \| --- \| |

**Measures taken by the interviewer**

| **1** | Indicate if child attends morning, afternoon, or evening class | \| **⃞** \| Morning \| (1) \| **⃞** \| Afternoon \| (2) \| **⃞** \| Evening \| (3) \| \| --- \| --- \| --- \| --- \| --- \| --- \| --- \| --- \| --- \| |
| --- | --- | --- | --- | --- | --- | --- | --- | --- | --- | --- | --- |
| **2** | What is the sex of the child? | \| **⃞** \| Girl \| (1) \|  \| **⃞** \| Boy \| (0) \| \| --- \| --- \| --- \| --- \| --- \| --- \| --- \| |
| **3** | When is the child’s birthday? (dd/mm/aaaa) | \| **/ /** \| Age \|  \| *Don’t know* \| **⃞** \| \| --- \| --- \| --- \| --- \| --- \| |
| **4** | Weight of the child? | \|  \|  \| Kg \|  \| *(Not measured)* \| **⃞** \| \| --- \| --- \| --- \| --- \| --- \| --- \| |
| **5** | Height of the child? | \|  \|  \| Meters \|  \| *(Not measured)* \| **⃞** \| \| --- \| --- \| --- \| --- \| --- \| --- \| |
| **6** | Are the child’s fingernails dirty? | \| **⃞** \| Yes \| (1) \| **⃞** \| No \| (0) \| **⃞** \| *Don’t know* \| (99) \| \| --- \| --- \| --- \| --- \| --- \| --- \| --- \| --- \| --- \| |

